### Statistical analyses

A consultant group of statisticians has been appointed to conduct the statistical work for this study, including data completion, interim analysis, application of statistical technique and final assessment. The principal analysis will be an intention-to-treatment basis. For baseline characteristics, continuous variables are assessed using the Student *t *test and discrete variables are compared using the chi-square test. The two-sided null-hypothesis for the primary outcome measure states that usual and high dose valsartan lead to the same expected change of ventricular remodeling during the 12 months after MI. This null-hypothesis will be tested by application of an analysis of covariance that adjusts for age, gender, and cardiovascular risk factors. Primary outcome will be compared using 2-sample *t *tests. Event-free cumulative survival rates are plotted using the Kaplan-Meier method and comparisons are made between patients with and those without clinical events using the log-rank test. A Cox proportional hazards model with the use of forward selection based on the likelihood ratio test will be implemented for multivariate analysis to determine which prognostic factors identified in the univariate analysis were significantly related to 12-month clinical events. Assessments for the change of neurohormone and other echocardiographic indices will be compared between treatment groups at 12-month follow-up using 2-sample *t *tests.

We will compare proportions of missing data using chi-square tests and agreement between data collection methods using Lin's Concordance Correlation Coefficient. Additionally, sensitivity analyses will be conducted using different patient populations (per protocol population excluding patients with relevant protocol violations), different imputation techniques for missing values, and different statistical methods for taking into account covariates. A value of p < 0.05 will be considered statistically significant.

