## Methods and Design

### Study design

VALID is a prospective, multicenter, randomized, open-label, active controlled study with two parallel study groups. VALID is being conducted in 18 tertiary hospitals throughout South Korea. Participants are randomly allocated into the usual dose group and high dose group and followed-up for 12 months after discharge. Overall study algorithm is depicted in Figure 1. Baseline echocardiographic examination and neurohormonal assay are performed before discharge. Study approval was given by the institutional review board at each participating center, and consecutive, eligible patients are provided written informed consent.

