### Randomization

Randomization will take place following initial echocardiographic estimation of left ventricular ejection fraction, which is conducted after stabilization by reperfusion therapy or conservative treatment. Eligible patients are randomly assigned in a 1:2 ratio to receive the usual dose (valsartan 80 mg/day) or a high dose (valsartan up to 320 mg/day). Random allocation with stratified technique is generated automatically by a centralized web based tool (http://www.cnrres.co.kr/valid) so it cannot be influenced by researchers.

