### Outcomes measurement

The primary outcome of the study is the changes of the echocardiographic indices of LV remodeling, which is the LV volume index at end-systolic and end-diastolic time as measured by modified Simpson's rule [25], during the study period. Echocardiographic records from participating institute are sent to the core echocardiography laboratory for the analysis. Secondary outcomes include occurrence of predefined clinical events (all-cause death, cardiovascular death, hospitalization, revascularization), changes of plasma level of neurohormone (B-type natriuretic peptide, norepinephrine, aldosterone), and echocardiographic indices other than ventricular volume (ejection fraction, wall motion score index, mitral inflow, tissue Doppler index) at 12 months (Table 2). Neurohormone measurement will be conducted in a core laboratory.

**Table 2 T2:** Study Objectives

Primary Objective	Secondary objectives
Change in the LV index measured by echocardiography from baseline to follow-up	Change in functional capacity (NYHA class)

	All cause mortality

	Cardiovascular death

	Hospitalization

	Revascularization procedures (emergency and elective)

	Change in B-type natriuretic peptide (BNP) level

	Change in plasma norepinephrine level

	Change in serum aldosterone level

	Change in ejection fraction

	Change in MI index (wall motion score index)

	Change in sphericity index

	Change in mitral inflow index (mitral E/A ratio, mitral deceleration time)

	Change in tissue Doppler index (mitral Ea)

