### Sample size

The sample size calculation is based on the primary outcome and the primary analysis for the intention-to-treat population. In the VALIANT Echo study, [17] a sample size of 600 patients was determined necessary to detect, with a 90% power, a 7.6 mL difference in end-diastolic volume between the treatment groups. Because the present study enrolls more patients with mild degree (EF < 50%) LV dysfunction, we anticipate that the difference of ventricular volume between treatment groups will be smaller than the previous study. Thus, detection of 3.8 mL difference, with a two-sided level of significance α = 5% and a power of 1-β = 90%, in end-diastolic volume between treatment groups would require a sample size of 279 patients in a usual dose of valsartan group and 558 patients in a high dose valsartan group. Assuming 25% of patients are lost to follow-up or with missing data, as reported in the GISSI-3 study [27], the required sample size of this study will be a total of 1,116 patients. The study is likely to be underpowered in terms of assessing secondary outcomes if this size is employed. Variability data for the outcome measures could be used to inform design a subsequent larger-scale randomized controlled trial, if post hoc analysis reveals this study to be underpowered.

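### Neither analysis named for the primary outcome adjusts for baseline LV volume index, which gives up some precision and leaves part of any chance baseline difference in the estimate

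*Protocol article*

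**What the plan says.** Protocol article, Outcomes measurement: "The primary outcome of the study is the changes of the echocardiographic indices of LV remodeling", namely the end-systolic and end-diastolic volume indices. Table 2 defines the change as running from baseline to follow-up.

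Statistical analyses: the null hypothesis of equal expected change over 12 months is to be tested by "an analysis of covariance that adjusts for age, gender, and cardiovascular risk factors". The risk factors are not itemised. The next sentence gives a second method for the same outcome: "Primary outcome will be compared using 2-sample" t tests. Other ways of handling covariates appear only among the sensitivity analyses.

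Study design: "Baseline echocardiographic examination and neurohormonal assay are performed before discharge". Randomization: "Random allocation with stratified technique is generated automatically by a centralized web based tool". No stratification factor is named.

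Sample size: a 3.8 mL difference in end-diastolic volume, two-sided 5%, 90% power, requiring "279 patients in a usual dose of valsartan group and 558 patients in a high dose valsartan group".

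**The concern.** Baseline volume can be expected to be a strong predictor of 12-month volume, and the design already collects it. The article does not leave the covariates open. It lists them, and the list leaves out the baseline value of the outcome while admitting an undefined class of risk factors.

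A change score subtracts baseline with a fixed slope of 1. Where the true slope is smaller, this over-corrects. Two things follow. The treatment estimate has a larger variance than it needs, and part of any chance difference in baseline volume between the arms stays in it. The article plans t tests of baseline characteristics but states no way of acting on an imbalance in volume.

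**Working it through.** **Inputs.** From Sample size: difference 3.8 mL, two-sided 5%, 90% power, 279 and 558 evaluable. From Randomization: 1:2 allocation. The article gives no SD and no baseline-to-12-month correlation r. The SD is therefore back-solved, and r is assumed to lie between 0.5 and 0.9. The figures are in mL, as in the Sample size section, although the outcome is an index; the variance ratios have no units.

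**1. The plan's own figure.** √(1/279 + 1/558) = 0.07332, and 1.960 + 1.282 = 3.2415. The SD that gives 279 and 558 is 3.8 / (3.2415 × 0.07332) = 15.99 mL. The allowance for loss reproduces: 837 / 0.75 = 1,116.

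**2. Variance with baseline in the model.** Let both time points have variance s². An unadjusted change score has variance 2(1−r)s². ANCOVA on baseline has (1−r²)s². The ratio is (1+r)/2.

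**3. Power and sample size**, taking 15.99 mL as the SD of change. Power = Φ(3.8 / (15.99 × √ratio × 0.07332) − 1.960). The evaluable number for 90% power is rounded up within the usual-dose arm and multiplied by 3.

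| r (assumed) | ratio | power at 279/558 | evaluable for 90% power |
|---|---|---|---|
| no baseline term | 1.00 | 90.0% | 837 |
| 0.5 | 0.75 | 96.3% | 630 |
| 0.7 | 0.85 | 94.0% | 714 |
| 0.9 | 0.95 | 91.4% | 798 |

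**4. Chance imbalance.** With equal variances the slope of 12-month on baseline volume is r. A baseline difference d between the arms therefore leaves (r−1)d in the change-score estimate. The baseline SD is 15.99 / √(2(1−r)), and one standard error of d is that SD × 0.07332.

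- r = 0.5: SD 15.99, d = 1.17 mL, residual 0.5 × 1.17 = 0.59 mL, or 15% of 3.8 mL.
- r = 0.9: SD 35.75, d = 2.62 mL, residual 0.1 × 2.62 = 0.26 mL, or 7% of 3.8 mL.

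**5. Unequal variances.** If the 12-month SD is k times the baseline SD, the ratio becomes (1−r²)k² / (1 + k² − 2rk). At an assumed k = 1.2:

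- r = 0.5: 1.080 / 1.24 = 0.87
- r = 0.6: 0.9216 / 1.00 = 0.92
- r = 0.7: 0.7344 / 0.76 = 0.97

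The gain for r of 0.5 to 0.7 then shrinks from 25–15% to about 13–3%.

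**6. Could adjustment cure a power shortfall?** The Sample size section cites an earlier echocardiographic study: 600 patients, 7.6 mL, 90% power. Assuming two-sided 5% and equal arms, SD = 7.6 / (3.2415 × √(2/n per arm)). This gives 23.4 mL for three arms of 200 and 28.7 mL for two arms of 300. At 279/558 and 3.8 mL, power on those SDs is 59.9% and 43.8%. Baseline adjustment with r from 0.5 to 0.9 would lift these to 72.3–62.1% and 54.9–45.7%. Reaching 90% needs a ratio of (15.99/23.4)², about 0.465, or (15.99/28.7)², about 0.31. The smallest value of (1+r)/2 for r ≥ 0 is 0.5.

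**The case against.** **Baseline is already subtracted.** This stands in large part. The comparison of change scores is unbiased under randomisation and its type I error is controlled. Only the fraction (r−1) of a chance imbalance remains, not the whole of it. A reader might infer that the treatment estimate is biased; the documents do not support that.

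**The gain may be small.** This also stands. It is 5% of variance at r = 0.9 and shrinks further if volumes become more variable over follow-up, which is plausible because the Background describes enlargement whose extent differs among patients. The ratio is also taken against an unadjusted change score. It gives no credit for what age, gender and risk factors may already explain, so the gain over the stated ANCOVA could be less.

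**The strata.** A reader might infer that the randomisation strata are left out of the model. This cannot be asserted. The article names no stratification factor, and the factors could be age, gender or a cardiovascular risk factor, all of which the ANCOVA covers. An article may also leave that list to the full protocol.

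**The pre-randomisation echo.** Randomization places an initial echocardiographic estimate of ejection fraction before allocation, whereas Study design says only that the baseline examination precedes discharge. In the high-dose group, titration also begins before discharge. The article does not show that the two recordings are the same. This bears on which reading to use as the covariate, not on whether to use one.

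**Article versus analysis plan.** Detail may sit in a document not shown. But the article states a covariate list and then a second, unadjusted test, so the point rests on what is written.

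**Conclusion.** The point holds as a modest, nearly cost-free improvement to a stated method. Two analyses are named for the primary outcome, and neither contains baseline LV volume index. The loss is 25% to 5% of the variance of an unadjusted change score for r of 0.5 to 0.9, given equal variances. On the plan's own implied SD that is worth about 1 to 6 points of power.

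These sizes rest on an assumed r, on equal variances, and on reading the implied SD as the SD of change. The existence of a gain does not depend on the trial being underpowered.

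A reader might infer that baseline adjustment would rescue a trial short of power. It would not, on the same reading of the SD. The starting powers of 60% and 44% rest on an assumed number of arms in a study not at hand, and they raise a separate question about the sample size.

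**What to change.** Before any comparison between the arms, name one primary analysis: an ANCOVA of 12-month LV volume index (or its change; the treatment estimate is the same once baseline is in the model) on treatment, the baseline value of the same index, and a short fixed covariate list including age and sex. Either itemise the cardiovascular risk factors or drop them from the primary model. Keep the two-sample t test as supportive only.

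State the stratification factors and include those actually used, entering each once if it overlaps with age, sex or a listed risk factor.

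Take the baseline value from the core-laboratory reading, using the pre-randomisation recording where one is available, and say what is used where it is not.

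The cost is a change of wording and, at most, core-laboratory reading of recordings already made. No new patient assessment is needed.

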## Background

Progressive enlargement of the heart chamber and deterioration of contractile function after myocardial infarction (MI), termed post-MI ventricular remodeling, is associated with development of heart failure and poor prognosis [1-3]. The magnitude of post-MI remodeling is influenced by several determinants, most notably infarct size [4], but also by ventricular wall stress [5], patency of infarct-related artery [6], and a number of neurohormonal factors [7]. Thus, the consequence of post-MI remodeling varies among patients with acute MI even in the era of reperfusion therapy [8]. Modification of neurohormonal acitivities, particularly the rennin-angiotensin-aldosterone system (RAAS), can significantly influence the process of ventricular remodeling after acute MI. Suppression of angiotensin activity either by inhibition of angiotensin-converting enzyme (ACE) [9-11] or by blockade of angiotensin II receptor [12] attenuates ventricular dilatation and improves clinical outcomes. Based on the results from major pivotal clinical trials, it is usually recommended in practical guidelines that the maximal clinical dose of ACE inhibitors used in those trials be given to patients after acute MI [13,14]. A seminal finding that the neurohormone level is linearly related with mortality [15] in patients with heart failure also suggests the potential benefit of higher doses.

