### Patient population

Men and women aged 18 years or older who suffer their first acute ST-elevation myocardial infarction with the sign of LV dysfunction are eligible for this study (Table 1). In the present study, LV dysfunction is defined as an ejection fraction < 50% using a modified Simpson's rule [25]. Enrollment criteria are intended to include patients in acute stage of infarction, within 10 days of symptom onset, who are typically treated under modern therapeutic strategy. Patients are recruited regardless of whether they received reperfusion therapy, either thrombolysis or primary percutaneous coronary intervention, or not. Pharmacological therapy other than study drug, including beta-adrenergic blockers, is allowed according to the discretion of attending physician. Patients who have contraindication to the study drug or major concomitant disease are excluded (Table 1).

**Table 1 T1:** Eligibility criteria

Inclusion criteria	Exclusion criteria
Subjects > 18 years of age	Contraindication for use of ARB

Either gender	Urgent need for revascularization procedure

First episode of acute MI	Severe heart failure (NYHA IV or need for inotropic support)

Typical pain lasting ≥ 20 minutes	Persistent (>1 hour) severe hypotension (systolic blood pressure < 90 mmHg)

ST elevation of more than 1 mm in at least 2 separate leads on the ECG	Refractory or potentially lethal arrhythmias

An echocardiographic LV EF < 50%	Hemodynamically significant right ventricular infarction

Optimal recording of echocardiographic imaging of apical chamber views	Congenital heart disease

Patients who provide written informed consent	Primary valvular disease, severer than mild degree

	Idiopathic hypertrophic cardiomyopathy

	Concomitant inflammatory cardiomyopathy

	Significant renal dysfunction (serum creatinine 2.5 mg/dl)

	Significant hepatic dysfunction (serum transaminase more than 3 times normal)

	Anemia (hemoglobin < 10 mg/mL or 6 mmol/L)

	Psychiatric disorders, alcohol or drug abuse

	Life expectancy is less than 1 year

	Participation in any other pharmacological study within 2 months

	Refusal or inability to provide informal consent

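### The analyses stated for the primary outcome name no baseline measure of infarct extent, although the protocol calls infarct size the leading determinant of remodeling; a modest, nearly free gain in precision is forgone.

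*Protocol article*

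**What the plan says.** All references are to the protocol article.

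- **Statistical analyses, adjusted test.** The primary null hypothesis is to be tested with an ANCOVA that "adjusts for age, gender, and cardiovascular risk factors". The risk factors are not itemised.
- **Statistical analyses, unadjusted test.** The next sentence reads "Primary outcome will be compared using 2-sample" t tests. The article does not say which of the two decides the trial.
- **Statistical analyses, sensitivity.** Analyses with "different statistical methods for taking into account covariates" are planned, with no covariates named.
- **Background.** "The magnitude of post-MI remodeling is influenced by several determinants, most notably infarct size"; ventricular wall stress, patency of the infarct-related artery and neurohormonal factors follow.
- **Outcomes measurement, Table 2.** Change in the wall motion score index, labelled there as the MI index, is a secondary objective. Recordings go to a core echocardiography laboratory.
- **Study design and Randomization.** A baseline echocardiogram is done before discharge. Randomization follows an initial echocardiographic estimate of ejection fraction, after reperfusion or conservative treatment.
- **Patient population.** "Patients are recruited regardless of whether they received reperfusion therapy".

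**The concern.** The covariates named for the primary outcome describe the patient's general risk. The Background says that the outcome is driven mainly by the infarct itself. An itemised list of cardiovascular risk factors would ordinarily hold such things as hypertension or diabetes, so spelling the phrase out later would not naturally bring in infarct extent.

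Variation in 12-month volume change that comes from infarct extent therefore stays in the residual error, although a baseline index of regional wall motion has to be collected for a secondary outcome. What is at stake is the precision of the dose contrast, together with the chance to adjust for accidental imbalance in a strong prognostic factor. If the t test is the deciding analysis, no covariate helps at all, so the two sentences on the primary outcome have to be settled together.

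**Working it through.** **Inputs from Sample size:** difference 3.8 mL in end-diastolic volume, two-sided α = 0.05, power 90%, 279 evaluable patients on the usual dose and 558 on the high dose, 25% loss. No SD is given. The outcome itself is a volume index; the figures below stay on the mL scale of the sample size calculation.

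**1. The plan's own figure.** 279 + 558 = 837, and 837 / 0.75 = 1,116. The loss step reproduces exactly. The 279 and 558 cannot be checked independently without an SD, so the SD is solved backwards:

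- SE = 3.8 / (1.960 + 1.2816) = 1.172 mL
- SD = 1.172 / √(1/279 + 1/558) = 15.99 mL
- 95% half-width = 1.960 × 1.172 = 2.30 mL

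These numbers are consistent with an unadjusted comparison of two means, and no covariate credit is stated.

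**2. Effect of an added baseline covariate.** Let R² be the further share of outcome variance that it explains. Then residual SD = 15.99 × √(1 − R²), the half-width shrinks by the same factor, and power = Φ(3.8/SE − 1.960). R² is assumed, because the documents do not give it.

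| R² (assumed) | Residual SD (mL) | 95% half-width (mL) | Power |
|---|---|---|---|
| 0 | 15.99 | 2.30 | 90.0% |
| 0.05 | 15.58 | 2.24 | 91.4% |
| 0.10 | 15.17 | 2.18 | 92.7% |
| 0.20 | 14.30 | 2.06 | 95.2% |

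**3. The same gain by recruitment.** Extra enrolment = 1,116 × (1/(1 − R²) − 1), which is about 59 patients at R² = 0.05 and 124 at 0.10.

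**4. Sensitivity to the SD.** The reference design in Sample size (600 patients, 7.6 mL, 90% power) implies a larger SD: 7.6 / (3.2416 × √(2/n)) is 23.4 mL with 200 per group or 28.7 mL with 300. That section does not state the number of groups. At 279 and 558, power would then be 59.9% or 43.8% unadjusted, 62.1% or 45.7% at R² = 0.05, and 64.4% or 47.7% at R² = 0.10. The benefit of adjustment is somewhat larger there, but the SD is a separate and bigger question that this point does not settle.

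**The case against.** The strongest reply is that nothing here is wrong. Leaving a prognostic covariate out of a randomised comparison keeps the test valid and the estimate unbiased. The p-value already allows for chance imbalance. The Background describes biology and makes no commitment about the model, so there is no contradiction. The risk factors and the stratification factors are not itemised, and an analysis plan not shown may extend the list. All of this stands, and it limits the point to efficiency. It does not remove it: the article does state the character of its covariates, and infarct extent is not among them.

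Other limits also stand:

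- **Reperfusion.** A reader might infer that the protocol names reperfusion as a driver of remodeling and measures it at the baseline echo. It does neither. The Background names patency of the infarct-related artery, the Conclusions link reperfusion only to better preserved contractile function, and no section says that reperfusion status is a recorded field.
- **Wall motion score index.** It is a proxy. Table 2 calls it the MI index, but nowhere is it described as a measure of infarct size.
- **Overlap.** The index and the LV volumes come from the same examination. Baseline LV volume is also absent from the stated list and is probably the stronger covariate. Once it is included, the further R² from wall motion could be below 5%.

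**Conclusion.** The point holds as a modest improvement in efficiency. With an assumed further R² of 5% to 10% and the implied SD of 16.0 mL, it is worth 1.4 to 2.7 percentage points of power and 0.06 to 0.12 mL of half-width. The lower end, or less, is the more plausible once baseline volume is adjusted for. The 20% row in the table is shown for range only and should not be relied on.

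Two stronger readings are tempting. One is that the primary comparison is biased by the omission; randomisation rules that out. The other is that the trial falls short of its stated 90% power because of the covariate list; the sample size takes no covariate credit, so adjustment would add to that figure and does not restore anything missing from it.

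**What to change.** In Statistical analyses, rewrite the two sentences on the primary outcome together:

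1. Name the ANCOVA as the single primary analysis and make the two-sample t test supportive.
2. Add to its prespecified covariates the baseline value of the LV volume index being analysed and the core-laboratory wall motion score index, as a continuous variable. Both should come from the echocardiogram made before randomisation. The wording should say so, because Study design places the baseline examination only before discharge.
3. Add reperfusion status at entry (primary PCI, thrombolysis, none) if the case report form records it.
4. Fix the list before any by-arm data are seen, and state how missing baseline values are handled.

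The cost is a few lines of wording and at most four degrees of freedom (one for each echo covariate, two for reperfusion) among about 837 evaluable patients. No new echo measurement should be needed, since change in both echo indices already requires a baseline value.

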**Figure 1 F1:**
[figure not shown]
**Overall study algorithm of the VALID study**. This figure illustrates the study algorithm. A total of 1116 patients will be randomly allocated into the usual dose group (n = 372) and high dose group (n = 744) and followed-up for 12 months after discharge.

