### Adverse effects

Analysis of safety related data is performed with respect to frequency of serious adverse events, stratified by causality and intensity of morbidity in both treatment groups.

Patients are interviewed at each visit about the occurrence of any adverse events, including the time of onset, duration, and severity; all information is recorded on a case report from. The causal relation to the study drug and the intensity of adverse events are evaluated by the investigators. Serious adverse events (SAE) have to be reported to the institutional review board and study sponsor by the principal investigator within 24 hours after the SAE becomes known.

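### The log-rank test for clinical events is specified between patients with and without events, not between dose groups, so no stated analysis guarantees a valid dose comparison for these secondary outcomes

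*Protocol article*

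**What the plan says.** Under Outcomes measurement the article makes clinical events secondary outcomes: "Secondary outcomes include occurrence of predefined clinical events (all-cause death, cardiovascular death, hospitalization, revascularization"). Table 2 lists the same four among the secondary objectives. The trial has one randomised contrast, described in the Figure 1 legend: "A total of 1116 patients will be randomly allocated into the usual dose group (n = 372) and high dose group (n = 744").

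Three sentences under Statistical analyses matter here:

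- **Log-rank test.** After the Kaplan-Meier curves, "comparisons are made between patients with and those without clinical events using the log-rank test".
- **Cox model.** "A Cox proportional hazards model with the use of forward selection based on the likelihood ratio test will be implemented for multivariate analysis", whose stated aim is "to determine which prognostic factors identified in the univariate analysis were significantly related to 12-month clinical events". Neither the candidate factors nor randomised dose is mentioned.
- **Other secondary outcomes.** "Assessments for the change of neurohormone and other echocardiographic indices will be compared between treatment groups at 12-month follow-up using 2-sample" *t* tests.

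The section closes with a general threshold: "A value of p < 0.05 will be considered statistically significant". Under Adverse effects, the frequency of serious adverse events is to be reported "stratified by causality and intensity of morbidity in both treatment groups". This is a safety tabulation and gives no test or effect estimate for the predefined events.

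**The concern.** A log-rank test needs groups that are fixed before the outcome is known. Here the outcome itself forms the groups, so the result is settled in advance and says nothing about dose. The Cox model does not close the gap, because its declared aim is to find prognostic factors and the randomised comparison is not tied into it.

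At stake is the between-dose evidence on death, cardiovascular death, hospitalisation and revascularisation. Followed literally, the text yields an uninformative significant log-rank result and perhaps no hazard ratio for high versus usual dose. A dose hazard ratio that appears only when it is significant would also mislead anyone using it to plan a later, larger trial.

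**Working it through.** **1. Inputs.** From the article: 372 usual-dose and 744 high-dose patients, 12 months of follow-up, significance at 0.05 (taken as two-sided). The article gives no event rate and no hazard ratio for events, so there is no figure of its own to reproduce. Assumed for illustration: a single time-to-first-event outcome, a 12-month usual-dose rate of 10% or 20%, hazard ratios (HR) of 1.0, 0.8 and 0.7, and exponential event times. The circularity in steps 2 and 3 does not depend on the rates or hazard ratios.

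**2. The curves.** Patients without events never contribute an event, so their curve is 100% throughout. Every patient with an event contributes one, so that curve reaches 0 by month 12. Both hold under any dose effect, including none.

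**3. The log-rank statistic as worded.** Take N = 1116 patients, D of whom have an event, with the rest followed to month 12. At the k-th event, D − k + 1 of the N − k + 1 patients at risk belong to the event group, so p_k = (D − k + 1)/(N − k + 1). Then O = D, E = Σp_k, V = Σp_k(1 − p_k), and χ² = (O − E)²/V, against a critical value of 3.84.

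- D = 1: E = 1/1116, V = (1/1116)(1115/1116), χ² = 1115.
- D = 112 (10% of 1116): E = 5.87, V = 5.47, χ² = (112 − 5.87)²/5.47 ≈ 2060.
- D = 223 (20%): E = 24.0, V = 20.7, χ² ≈ 1912.

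The statistic is enormous even with a single event. Simulation (2,000 runs per scenario) agrees:

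| HR | Usual-dose rate | Expected events | Rejects, by event status | Rejects, by dose |
|---|---|---|---|---|
| 1.0 | 10% | 111.6 | 100% | 5.3% |
| 1.0 | 20% | 223.2 | 100% | 5.0% |
| 0.8 | 10% | 97.3 | 100% | 19.6% |
| 0.8 | 20% | 196.0 | 100% | 35.4% |
| 0.7 | 10% | 90.1 | 100% | 38.0% |
| 0.7 | 20% | 182.0 | 100% | 64.8% |

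**4. What the Cox model can offer on dose.** Suppose dose is a candidate and is kept only when p < 0.05.

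- *Expected events at HR 0.8:* 372 × 0.10 + 744 × (1 − 0.90^0.8) = 37.2 + 60.1 = 97.3 at the 10% rate; 74.4 + 121.6 = 196.0 at the 20% rate.
- *Standard error of the log HR:* 1/√(D × 1/3 × 2/3) = 0.215 and 0.152.
- *Chance of being dropped:* by the simulated rejection rates, 1 − 0.196 ≈ 80% and 1 − 0.354 ≈ 65%.
- *Exaggeration:* a retained benefit must have an HR below exp(−1.96 × SE), which is 0.66 or 0.74. Every retained beneficial estimate therefore overstates a true 0.8.
- *Coverage when retained (normal approximation):* dose is retained with probability 0.1796 or 0.3134, of which 0.1782 or 0.3131 is in the direction of benefit. Estimates more than 1.96 SE below the truth (probability 0.025) miss it, and so do those retained in the wrong direction. Coverage is (0.1782 − 0.025)/0.1796 ≈ 85% and (0.3131 − 0.025)/0.3134 ≈ 92%. The same calculation at HR 0.7 gives about 93% and 96%, so the shortfall belongs to the low-power settings.

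A separate simulation of a univariate screen plus forward selection (800 runs; assumed 12% baseline risk, five covariates, 0.05 thresholds) gave the same picture at HR 0.8: dose retained in about 20% of runs, mean retained HR about 0.63, coverage about 86%. With no dose effect, dose was retained and significant in 4.8% of runs.

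**5. After the correction.** The by-dose log-rank test holds its level but has little power. By Schoenfeld's formula, 80% power needs 710 events at HR 0.8 or 278 at HR 0.7, against about 90-196 expected for those hazard ratios. An observed HR of 0.8 would carry a 95% CI of exp(ln 0.8 ± 1.96 × SE): 0.52 to 1.22 with 97 events, or 0.59 to 1.08 with 196.

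**The case against.** The strongest reply is that this is a slip of the pen. The trial has one randomised contrast, neighbouring outcomes are compared by treatment group, and the appointed statisticians would hardly run the sentence literally. That is plausible and bears on severity. It does not remove the point. The text states a specific comparison and the comparison is wrong, so neither a fuller analysis plan nor the brevity of an article excuses it. The Cox sentence that follows also omits dose.

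The second reply is that events are secondary. The Sample size section concedes low power for secondary outcomes, and the Discussion gives the small expected clinical differences as a reason for an echocardiographic surrogate. This stands and lowers the severity. It also makes an interval more useful than a test that will rarely be significant.

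Two stronger readings are tempting and should be resisted:

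- **That no planned analysis can give the dose effect on events.** A reader might infer this, but the Cox candidates are not listed and nothing excludes dose. A candidate list may properly sit in an analysis plan, and searching for prognostic factors is a legitimate separate aim. What the text supports is that no stated analysis *guarantees* a valid between-dose estimate.
- **That forward selection invalidates the dose p-value.** Over all trials, false positives stayed at 4.8% in the null simulation. The damage is to the hazard ratio and interval reported after selection.

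**Conclusion.** The log-rank comparison is wrong as written: it rejects in essentially every trial and carries no information about dose. This follows from how the groups are defined and needs no assumption about event rates. The Cox model is a weaker, secondary part of the point. It may report dose, but under the assumed rates and HR 0.8 it would drop dose in about 65-80% of trials. When dose is kept, the estimate is exaggerated and interval coverage is about 85-92%. Those figures rest on the assumed rates, hazard ratios and 0.05 retention rule, none of which the article gives for events.

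This should be fixed, but it does not threaten the trial. The primary hypothesis, the sample size and the primary echocardiographic analysis do not depend on it.

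**What to change.** Replace the log-rank sentence and separate the two aims of the Cox modelling, for example:

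> Event-free survival will be shown by Kaplan-Meier curves for each randomised dose group in the intention-to-treat population and compared between dose groups with a log-rank test. The hazard ratio for high versus usual dose, with its 95% CI, will come from a Cox model in which dose group is always included. A forward-selected model of prognostic factors will be reported separately as exploratory.

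Stratifying the log-rank test or the Cox model by the randomisation factors is optional. The Randomization section mentions a stratified technique but names no factors, and an unstratified comparison by dose already cures the circularity.

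The cost is a few lines of analysis text, with no new data, visits or patients. The change should be dated and made before events are analysed by dose.
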